## Abstract

**Background:**

Farmers in Indonesia have a high risk for hypertension owing to their lifestyle and working environment. Diet management is a solution to reduce hypertension, and Indonesia has natural resources in the agricultural sector that could help manage hypertension. Optimizing vegetable and fruit intake in a plant-based diet (PBD) could help maintain blood pressure among farmers in Indonesia.

**Objective:**

This study aims to explore the health problem of hypertension and the characteristics of local food sources to formulate a PBD menu for treating hypertension, as well as assess the prevalence of hypertension, level of acceptability of a PBD, and associated sociodemographic factors. Further, we want to examine the effectiveness of a community-based nursing program for managing hypertension using a PBD.

**Methods:**

We will use the exploratory sequential mixed methods approach. There will be a qualitative study (phase I) in 2022 and a quantitative study (phase II) in 2023. We will analyze data using a thematic framework in phase I. In phase II, the study will involve (1) questionnaire development and validation; (2) examination of the prevalence of hypertension, the level of acceptability of a PBD, and the associated factors; and (3) a randomized controlled trial. We will recruit farmers with hypertension who meet the study criteria. Moreover, in phase II, we will invite expert nurses and nutritionists to assess the face and content validity of the questionnaire. We will use multiple logistic regression models to estimate the associated sociodemographic factors and the level of acceptability of a PBD. Furthermore, a linear generalized estimating equation will be used to estimate the parameters of a generalized linear model with a possible unmeasured correlation between observations from different time points for systolic and diastolic blood pressure.

**Results:**

A model PBD for hypertension management is expected to be developed. In 2022, we will collect information on hypertension and the characteristics of local food sources for managing hypertension, and will formulate a PBD menu to treat hypertension among farmers. In 2023, we will develop a questionnaire to assess the acceptability of a PBD to manage hypertension among farmers, the prevalence of hypertension, and the sociodemographic factors associated with hypertension among farmers. We will implement a community-based nursing program for managing hypertension using a PBD among farmers.

**Conclusions:**

The PBD model will not be readily available for other agricultural areas since validation of local food variation is required to design the menu. We expect contributions from the local government to implement the intervention as one of the policies in the management of hypertension for farmers in the agricultural plantation areas of Jember. This program may also be implemented in other agricultural countries with similar problems, so that hypertension can be optimally treated among farmers.

**International Registered Report Identifier (IRRID):**

PRR1-10.2196/41146

## Introduction

Hypertension contributes to 12.8% of the total 7.5 million deaths worldwide [1]. The prevalence of hypertension in Indonesia is 33.4% [2], while in East Java province, it is 20.43% [3]. Farming communities have a high risk of health problems [4], including hypertension [5-7]. Hypertension among farmers in Indonesia has reached 36.1% [8]. Our previous study found that the incidence of hypertension among farmers in agricultural areas was 35.8% [9]. This shows the magnitude of the problem of hypertension among farmers, and there is a need for the management of care using an agricultural health nursing (agronursing) approach to realize the health status of farmers.

Agronursing can facilitate occupational health and safety among farmers [9]. Farmers’ health problems are generally caused by a lack of knowledge and skills in health management, which can lead to hypertension [10]. Most farmers with hypertension have a low level of education, so skills in self-care management are lacking [11]. Hypertension among farmers is also caused by an unhealthy lifestyle [9] and inadequate nutrition [12]. High consumption of unhealthy foods among farmers, such as high-sodium foods [6], and low knowledge about diet [13] can increase the risk of hypertension in farmers. Therefore, dietary management with a plant-based diet (PBD) needs to be introduced, and the basic principles of hypertension nursing care for farmers need to be developed.

Natural agricultural resources should be considered in the management of hypertension among farmers. The basic principles of hypertension care among farmers should be developed through optimizing the agricultural sector’s potential by consuming a PBD that prioritizes vegetables and fruits [14]. Therefore, it is necessary to formulate the basic concepts and principles of a PBD in nursing care management for farmers with hypertension based on the agronursing approach.

The agronursing approach to treat hypertension among farmers focuses on promotive and preventive measures to reduce the risk of disease occurrence or disease worsening from previous conditions [15]. Moreover, it focuses on the health status of individuals in carrying out their work (in this case, farmers who work in fields) in order to improve overall health (physically, mentally, and socially) [16]. The PBD concept is expected to be able to overcome the problem of hypertension among farmers in agricultural areas, which is synergistic with the culture and local wisdom of the agricultural population. Therefore, the objectives of this study are as follows: (1) to explore the health problem of hypertension among farmers and the characteristics of local food sources of vegetables and fruits that can be used in a PBD to manage hypertension; (2) to examine the prevalence of hypertension, the level of acceptability of a PBD, and the associated factors among farmers; and (3) to examine the effectiveness of a community-based nursing program for the management of hypertension using a PBD among farmers.

## Methods

### Study Overview

The exploratory sequential mixed methods approach will be used to achieve the research objectives in the following 2 phases: qualitative study (phase I) and quantitative study (phase II) (Figure 1). In phase I, we will explore the health problem of hypertension among farmers and the characteristics of local food sources of vegetables and fruits that can be used in a PBD to manage hypertension through semistructured interviews. Then, we will formulate a PBD menu to treat hypertension among farmers.

In phase II, we will conduct a quantitative study. In this phase, the following 3 activities will be performed: (1) we will develop and validate a questionnaire as the assessment instrument; (2) we will examine the prevalence of hypertension, the level of acceptability of a PBD, and the associated sociodemographic factors among farmers; and (3) we will examine the effectiveness of a community-based nursing program for managing hypertension using a PBD among farmers.

This study will use farmers with hypertension and their families in the planning of phases I and II.

**Figure 1 figure1:**
[figure not shown]
Study overview. COSMIN: consensus-based standards for the selection of health measurement instruments; Posbindu PTM; Pos Pembinaan Terpadu Penyakit Tidak Menular.

### Phase I: Qualitative Phase

#### Overview

We will perform a semistructured interview involving farmers with hypertension and the family members of eligible participants to address the research objectives. The qualitative study will provide insights on health problems related to hypertension and the characteristics of local food, and will help formulate a PBD to control blood pressure from the perspective of agricultural health nursing care services. After undergoing training in conducting qualitative studies, 5 investigators (TS, HR, FK, IR, and [name]) will conduct interviews in the field.

#### Setting

This study will recruit eligible participants selected from 3 public health centers (PHCs) in Jember, East Java Province of Indonesia. Jember, East Java Province is a province representing Indonesia’s agricultural sector. It is known that Jember Regency is an agricultural area, and most of its people make a living as farmers or work in agriculture. The agricultural land in Jember Regency is very fertile. Therefore, most land in Jember Regency is used for agriculture and plantations. This is very suitable as the main livelihood of the people of Jember Regency is related to the agricultural sector.

Jember Regency is considered one of the rice barns of East Java Province, reflecting that the agricultural sector plays an important role (leading sector) in the economy of Jember Regency, and it can be said that Jember has an agrarian economic structure. Since Jember’s economy is generally based on agriculture, the maintenance and management of natural resources are very important, and it is hoped that the economic development carried out is oriented toward environmentally sound development. Regarding cultivations, all areas except the city center have food crops; the slopes of Mount Argopuro have plantations of tea, coffee, cocoa, and rubber; the slopes of Mount Raung have plantations of coffee and tobacco; and central to southern areas have plantations of tobacco, sugarcane, and coconut. In Jember, 42.9% of the population has jobs in agriculture [17]. Based on data [18] released by BPS Kabupaten Jember, the population of Jember Regency in 2020 was projected to reach 2,536,729 people, consisting of 1,264,968 male residents and 1,271,761 female residents, and the population density in Jember Regency in 2020 reached 770.26 people/km^2^.

#### Participants

The inclusion criteria for recruiting the purposive sample are as follows: (1) farmers aged 20-65 years from other parts of East Java Province, Indonesia (citizens) living in 3 PHCs of Jember; (2) residents living in 3 PHCs of Jember; (3) those with hypertension; (4) those who consume fruits and vegetables to control their blood pressure; (5) those who attend the Integrated Health Center (IHC) for noncommunicable diseases (NCDs) in the community; and (6) those having and living with family for care provision. We will exclude older people who are not citizens of Indonesia and those who are unwilling to be interviewed or unable to communicate clearly due to language problems. To obtain more insights on the acceptability of a PBD, the family members of eligible farmers with hypertension will be included in the interview. The inclusion criteria are as follows: (1) employment as a farmer; (2) age 45-65 years; (3) presence of grade I/II hypertension according to the Eighth Joint National Committee on Prevention, Detection, and Treatment of High Blood Pressure (JNC VIII) criteria; and (4) presence of relatives who stay in the same house with their parents or take care of their parents by helping them with preparing food or assisting them in daily routines. We will exclude farmers with hypertension having other chronic diseases (diabetes mellites, chronic kidney disease, heart disease, and stroke).

#### Sampling Process

Phase I is estimated to last 3 months. The snowball sampling method will be used to recruit participants. The investigators (TS, HR, FK, IR, and [name]) will recruit participants in Jember based on the inclusion and exclusion criteria. The interviewees will be asked to recommend other eligible participants among farmers and their family members who wish to participate in this research. Investigators will contact eligible participants to explain the study details, confirm their interest in participating, and determine their preferred interview method (eg, individual interview or focus group discussion). Payment of US $10 will be made to participants for participating in this study (online transfer to their bank accounts).

#### Data Collection

Phase I will involve the following 2 data collection methods: in-depth interviews and focus groups using semistructured interview guides. Further, in-depth interviews may be conducted with certain respondents who have attended the previous focus group interviews to gain more perspectives and clarify the focus groups’ findings. Each focus group will consist of 4 to 6 participants. An earlier scoping review conducted by the same research team will help identify health problems related to hypertension among farmers. Then, we will explore the characteristics of local food sources to manage hypertension and formulate a PBD. The findings will provide additional information for developing the interview guides and questions (eg, “Can you describe your health problem related to your hypertension?” “How would you control your blood pressure with a plant-based diet?” “What kinds and contents of local foods would you use for controlling hypertension?” “How would you formulate a plant-based diet menu to control hypertension?” “What do you expect from a plant-based diet?” and “Would you adopt a plant-based diet? If yes, why? If no, why not?”). The preliminary semistructured interview guides, which contain open-ended questions and probes to explore the acceptability of a PBD, will be pilot tested.

We plan to interview the farmers and the family members of eligible farmers with hypertension. We will recruit 30 participants initially, but the final sample size for this qualitative study will be determined when data saturation is reached, for example, when additional data collection reveals no substantial new information. Each in-depth interview will take between 30 and 45 minutes, and the focus group interview will take around 45 to 60 minutes. Before the interviews, participants will provide their sociodemographic and related information, such as age, education, occupation, income, insurance, and health condition. Information about this research, including the hypertension problem and the characteristics of local foods used in a PBD, will be explained to all participants in Bahasa Indonesia before they are asked to provide informed consent. All interviews will be conducted in the Bahasa Indonesia language and will be audio recorded. Investigators will take down field notes, and transcripts will be translated line by line into English. All data will be translated into English to allow discussions with non-Indonesian researchers.

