### Phase II: Quantitative Phase

#### Activity 1: Questionnaire Development and Validation

##### Overview

In activity 1, we will develop a questionnaire of an acceptable PBD for controlling hypertension, according to the qualitative data in phase I. The quotations from raw data will become questionnaire items, themes will become scales, and codes will become variables. A Likert score will be used for measurement (range of 1 to 4 points), which will determine the levels of expectations and acceptability. Based on the scores of the items or the summed scores, expectations and acceptability can be categorized into the following 3 categories: affordable, accessible, and achievable. Categorization will be performed using a statistical formula. If the data are normally distributed, the grade level will be based on the mean value; otherwise, the median will be used (X < mean/median – 1 SD; mean/median – 1 SD < X < mean/median + 1 SD; mean/median + 1 SD < X).

The questionnaire will have the following 2 sections: (1) sociodemographic characteristics of hypertension and (2) acceptable PBD for controlling hypertension. The instructions and descriptions of the definition, concept, and criteria of a PBD will be provided at the beginning of the questionnaire. The Pender Health Promotion Model will guide the questionnaire’s qualitative analysis and item design. After performing a member check and assessing face and content validity with an expert committee, we expect the final version of the questionnaire. The expert committee will include investigators with expertise in qualitative research (HR), statistical analysis (FK), public health (TS), and research methodology ([name] and IR).

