### Ethical Considerations

This study has received ethical approval from the Ethics Committee for Research Involving Human Subjects, Faculty of Dentistry of Universitas Jember (approval number: 1548/UN25.8/KEPK/DL/2022, with an amendment on June 29, 2021) and conforms to the requirements of the World Medical Association’s Declaration of Helsinki. All the participants will provide written informed consent before their inclusion.

This study will use descriptive analytics in health and community service units with a quantitative approach through surveys and qualitative interviews at health and community service units. This research will not cause harm to the participants. Each participant will provide informed consent. We will give autonomy rights to prospective participants. Participants will be provided an explanation of the study, including the objectives, benefits, implementation process, and participant rights. Participants will be informed that there is no risk of harm if they do not participate in the study or leave the study while the research process is in progress.

The study will pay attention to safety aspects for both the researchers and participants, and will be performed according to the applicable COVID-19 protocol. The interviews will be adjusted according to the participants’ time. Participants will receive compensation (transportation fee) and food for each data collection. The design of this study involves an intervention group and a control group, and we will try to minimize the occurrence of unwanted incidents during the implementation of the intervention. We will provide leaflets containing educational materials for a PBD when the last measurement is taken. Participants in the control group will be offered a discussion session after reading the leaflet provided, but there is no compulsion to join the discussion session. All participants in the intervention group will receive the same intervention regardless of ethnicity, religion, and race.

The confidentiality of the participants’ data will be maintained, and the identity of the participants will not be disclosed. The data obtained will only be used for research purposes. To keep participants’ data confidential, the survey sheet will have a special code that does not display the personal data. Moreover, a statement will be provided that qualitative study data are anonymous or deidentified. Furthermore, a brief description of the protections in place will be provided.

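### Phase I explains the characteristics of local foods to every participant before asking which local foods they would use, so the answers on foods may partly echo the investigators' briefing

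*Protocol article*

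**What the plan says.** The Phase I Data Collection section describes what participants are told: "Information about this research, including the hypertension problem and the characteristics of local foods used in a PBD, will be explained to all participants". The same sentence places this "before they are asked to provide informed consent". Ethical Considerations adds: "All the participants will provide written informed consent before their inclusion".

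Among the sample interview questions in Data Collection is: "What kinds and contents of local foods would you use for controlling hypertension". Another asks how the participant would put together a plant-based menu to control hypertension.

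Objective 1 in the Introduction is "to explore the health problem of hypertension among farmers and the characteristics of local food sources of vegetables and fruits" that could serve in such a diet. The results are used twice. After the interviews, Study Overview says: "Then, we will formulate a PBD menu to treat hypertension among farmers". For the questionnaire, the Overview of Activity 1 says: "The quotations from raw data will become questionnaire items".

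**The concern.** An open question measures what a respondent would say unprompted only if the answer has not just been given. Here the food topic of the briefing is almost the same as the topic to be explored, and the briefing comes first. It is also given by, or on behalf of, the team that recruits and interviews, so participants have a social reason to repeat it.

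At stake is how far the food content from Phase I can be called the farmers' own. If part of it is the investigators' content returned to them, the menu and the acceptability items built on it would be credited to farmers more than they should be. Once the interviews are recorded, nobody can tell from the transcript alone which foods were volunteered and which were repeated.

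**Working it through.** The article gives no figure on this point and no calculation applies. The check is the order of steps and the overlap of content.

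**Order of steps**
1. Explanation to all participants, before consent (Data Collection).
2. Written consent, before inclusion (Ethical Considerations).
3. Interview or focus group with the open questions (Data Collection).
4. Menu formulated (Study Overview) and quotations turned into questionnaire items (Activity 1, Overview).

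Step 1 therefore precedes step 3 for everyone.

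**Overlap of content**
- Explained beforehand: the hypertension problem, and the characteristics of local foods used in the diet.
- To be explored under objective 1: hypertension as a health problem, and "the characteristics of local food sources of vegetables and fruits that can be used in a PBD to manage hypertension".
- Asked: of the six sample questions, two ask directly for food content (kinds and contents of local foods; how to formulate a menu). One asks about the participant's own health problem. The other three ask how the diet would be used to control blood pressure, what is expected of it, and whether it would be adopted.

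The overlap matters for the food questions. It matters little for the health-problem question, because a general account of hypertension does not supply a farmer's personal history.

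**Stated safeguards**
- Reflexivity, triangulation, peer debriefing and the audit trail (Qualitative Data Analysis Plan) act mainly at or after analysis.
- Respondent validation goes back to people who heard the same explanation.
- Pilot testing is described for the interview guides, not for the information given beforehand.
- The nurses and nutritionists in Validation and Reliability judge face and content validity. They are not asked whether an item began with a farmer or with the briefing.

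None of these separates foods volunteered from foods mentioned beforehand.

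**Extent**
Exposure covers all participants, initially 30. The effect cannot be computed. It could be nil if the script only names the topic, and larger if it describes particular foods and their properties.

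**The case against.** The strongest reply is that this is a consent sentence. Ethical Considerations requires the objectives to be explained, and objective 1 cannot be explained without naming local foods and hypertension. The article does not say that foods are listed or described, and the information script would normally sit in the full protocol. This stands in part. It rules out saying that the answers will echo the briefing, or that the answer is supplied before the question. It does not remove the point, because the sentence says that the characteristics of the foods are explained, which goes further than naming a topic. If only the topic is named, the sentence should say so.

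Second, participants are not blank slates. The Phase I criteria require farmers who already eat fruits and vegetables to control blood pressure. This stands and limits the likely effect, although the criterion is not stated for the family members who are also interviewed.

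Third, Phase I does not claim to be free of investigator input. A scoping review precedes it, and a theoretical model guides the analysis. The trial diet is described under Intervention as formulated by the researchers, drawing on a standard protocol from earlier studies. This also stands. The menu is not presented as purely farmer-derived, so the route from briefing to trial diet is only partial.

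Fourth, four of the six sample questions use the term plant-based diet, so participants need to know what it means. This is correct, and the fix has to allow for it.

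**Conclusion.** The point holds as a risk created by a stated step: food content is explained to everyone before the open questions that are meant to elicit it. Answers on foods may partly echo the briefing, and this may carry into the menu and into questionnaire items taken from quotations. The size is unknown. The conclusion assumes that the explanation conveys something about the foods, as the sentence says, and not merely the study topic.

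A reader might go further and infer that saturation will be reached early, or that every questionnaire item is contaminated. The article does not support either. Recruitment starts at 30, and absence of substantial new information is given only as an example of saturation. One questionnaire section is sociodemographic, and the other concerns acceptability and expectations and is not described as a food inventory. Nor does the point reach the trial's randomization, power or blood pressure analysis.

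It is still worth acting on, because the change is nearly free and the problem cannot be repaired once the interviews are done.

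**What to change.** Limit the information given before the interview to purpose, procedures, recording, risks and rights. Add a short generic definition of a plant-based diet, without local food examples or their properties, so that the questions using the term can be understood. Move any description of specific local foods to after the open questions, or to a debrief once recording has ended.

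If food content has to come first, record which foods were mentioned in the briefing and code separately those that participants volunteered unprompted. The menu and the questionnaire items can then be traced to one source or the other.

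The cost is a small rewording of the information script and moving one step. Participants have slightly less background before the interview.
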